### Data management and statistical analysis

All data will be stored via REDCap, an application specifically designed for the safe storage of clinical research data, for seven years. Only research personnel associated with the study will have access to the data and it will not be available to external agencies. Optotrak, IMU, and Pedar data will be coded so no personal information will be identified in the data. De-identified data will also be stored on a secure drive at the University. The patient’s gait kinematics are monitored as the project progresses to confirm no adverse effects of gait training, such as increased tripping risk. External auditing is not required in this study because all experimenters are trained to identify and record adverse events.

MTC data obtained from the treadmill walking will be analyzed using two intervention group comparisons and repeated measures ANOVA of the intervention groups and change scores, with post-hoc comparisons where relevant. Walking speed will be used as a co-variate due to its influence on MTC data. The between-subject factor will be treatment group (No-feedback and Feedback) with Time (pre-training baseline, post-training, one month, three months, and six months) being the within-subject factor.Between-group comparisons of MTC post-training will reveal effectiveness of the biofeedback gait training method in improving MTC.The within-subject analysis of the Feedback group will reveal the biofeedback effects on MTC by comparing each participant’s after intervention (post-training) data to that obtained in retention conditions, i.e. MTC data at one month (short-term retention) and at three months and six months (long-term retention).MTC data collected during overground walking during retention conditions will determine whether any changes in MTC are translated to overground walking.

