## Methods/Design

This single-blinded parallel group RCT with 1:1 randomization will assess the effects of biofeedback on MTC following gait training. It will conform to CONSORT guidelines and has been registered on the Australian and New Zealand Clinical Trials Registry (ANZCTR): ACTRN12617000250336. Ethics approval for the study was obtained from Austin Health, Melbourne Health, and Victoria University Human Research Ethics Committees. Informed consent procedures include the provision that participants clearly understand that they are free to withdraw at any time without providing a reason. The study design flowchart is shown in Fig. 1.

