### Sample size calculations

In determining sample sizes, for the between-group comparisons, to detect differences in MTC a medium effect size (ES = f = 0.25) between the group effects (No-Feedback versus Feedback) across the two time points (baseline and after training) a total of 126 or 63 per group is required (G*Power [25] calculation, 2 × 2 repeated measures design, α = 0.05, power = 0.85, correlation = 0.7). To allow a 20% drop-out, we shall initially recruit 75 participants per group (*N* = 150). This sample size will also allow detection of an increase of 1 SD in MTC of the biofeedback group, compared to their pre-training. The probability of tripping [7] calculated using the pilot (stroke) participants’ data suggests that a 1 SD (0.77 cm) increase in MTC will result in significant reduction in the risk of tripping on small (1–2 cm) obstacles. A 0.77-cm increase in MTC represents approximately a 50% gain in minimum ground clearance (mean MTC = 1.4 cm) that is shown by our modelling to represent a substantial decrease in tripping risk, i.e. the probability of contacting an obstruction of a given height.

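### The plan points to the post-training visit for judging effectiveness but lists several between-group tests of treadmill MTC without saying which one decides, and sizes the trial on yet another contrast

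*Protocol article*

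**What the plan says.** Under Data management and statistical analysis, the protocol article states that treadmill MTC "will be analyzed using two intervention group comparisons and repeated measures ANOVA of the intervention groups and change scores, with post-hoc comparisons where relevant". The ANOVA has treatment group as the between-subject factor and Time, with five levels from baseline to six months, as the within-subject factor.

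The same section then links analyses to questions. For effectiveness it says "Between-group comparisons of MTC post-training will reveal effectiveness of the biofeedback gait training method in improving MTC". Retention is assigned to within-group comparisons in the Feedback arm, and transfer to overground data.

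Under Primary outcomes, MTC is assessed at baseline and after training. Under Sample size calculations, the effect is defined as "a medium effect size (ES = f = 0.25) between the group effects (No-Feedback versus Feedback") and applied "across the two time points (baseline and after training) a total of 126 or 63 per group is required", with "α = 0.05, power = 0.85, correlation = 0.7".

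**The concern.** The time point is indicated consistently. The test is not. At least four between-group tests of whether biofeedback raises treadmill MTC fit the text:

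- the difference in post-training values;
- the difference in change from baseline;
- the group main effect over five visits;
- the Group x Time interaction.

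Post-hoc comparisons may follow. The sentence on effectiveness speaks of comparisons in the plural, and a raw post-training difference, a change-score difference and a contrast within the ANOVA all satisfy it.

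These tests do not estimate the same quantity. The five-visit group effect averages in the baseline visit, where randomisation implies no expected difference. The interaction responds to any difference in profile. If they disagree, the text gives no basis for saying which result is the trial's answer, and the choice could be made after the data are seen.

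**Working it through.** **Inputs from the sample size section.** f = 0.25, alpha 0.05, power 0.85, correlation rho = 0.7, two time points, 63 per group. For two groups d = 2f = 0.5.

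**Step 1: reproduce the stated N.** For the group effect in a repeated measures design with m = 2 visits, the noncentrality is N f² m / (1 + (m − 1) rho) = 126 × 0.0625 × 2 / 1.7 = 9.26, with 1 and 124 degrees of freedom. Power is 0.855, and N = 126 is the smallest even total that reaches 0.85. The Group x Time version of the formula gives N = 24. The stated N therefore belongs to the group effect averaged over baseline and post-training. That is not the post-training comparison, the change-score test or either test of the five-visit ANOVA.

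**Step 2: power of each candidate test.** Assume a true difference of 0.5 SD at post-training, none at baseline, 63 per group, and rho = 0.7 between all visits. For the t-tests, noncentrality = standardised difference × √(63/2).

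| Test | Standardised difference | Noncentrality | Power |
|---|---|---|---|
| Post-training value | 0.5 | 2.81 | 80% |
| Change score | 0.5/√(2 × 0.3) = 0.645 | 3.62 | 95% |
| Two-visit group effect (basis of N) | 0.25/√(1.7/2) = 0.271 | 1.52 | 33% |
| Five-visit group effect, effect at post-training only | 0.1/√(3.8/5) = 0.115 | 0.64 | 10% |
| Group x Time interaction, effect at post-training only | – | (63/2) × 0.25 × 0.8/0.3 = 21 (F test; 4 and 496 df) | 97% |

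A post-training comparison with baseline MTC as covariate has standardised difference 0.5/√(1 − 0.49) = 0.700, noncentrality 3.93 and power 97%.

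**Step 3: how often two of the tests disagree.** The correlation between the post-training and change-score statistics is (1 − 0.7)/√(2 × 0.3) = 0.387. In the normal approximation, the powers are 0.801 and 0.952 and both tests are significant in 0.776 of trials. They disagree in 0.801 + 0.952 − 2 × 0.776 = 0.20. Simulation of 20,000 trials gives 20.2%.

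**Step 4: false positives if any significant test counted.** Under no effect, the two tests in Step 3 are both significant in about 0.65% of trials, so at least one is significant in 10% − 0.65% = 9.4%. The table gives simulation results with 63 per group, five visits and each test at 0.05. The correlation structures, and values of rho other than 0.7, are assumptions.

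| Tests allowed to count | rho 0.7, equal correlation | rho 0.5–0.85, equal correlation | Correlation decaying with time |
|---|---|---|---|
| Post-training or change score | 9.4% | 9.4–9.6% | 9.1–9.5% |
| + interaction | 12.8% | 12.2–12.8% | 13.2–15.7% |
| + five-visit group effect | 14.6% | 13.8–14.8% | 16.3–17.6% |
| + unprotected tests at 1, 3 and 6 months | 19.7% | 17–21% | 21–23% |

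The decaying-correlation column has no sphericity correction. A single named comparison at post-training, whether raw, change-score or baseline-adjusted, has 4.7–5.5%.

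**The case against.** The strongest reply is that the plan already sets a priority. Only the post-training between-group comparison is tied to effectiveness, the primary outcome section uses baseline and post-training, and the sample size uses the same two visits. The post-training comparison can also be read as a contrast within the single Group x Time model. Post-hoc testing normally follows a significant omnibus test, and the later visits are assigned to retention. A test hierarchy is often left to the statistical analysis plan.

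Much of this stands. A reader might infer that the trial's false-positive rate is 9–14%, or that nothing is marked as deciding. The documents support neither. The 9–14% requires a rule that any significant test counts as success, and no such rule is stated. The time point is clearly indicated. Nor should the retention visits be counted as further chances at the same claim, so the 17–23% figures are an upper case only.

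What the reply does not settle is the test. The article does not stay silent and defer; it prescribes change scores, group comparisons and a five-visit ANOVA side by side for one outcome. The disagreement in Step 3 involves two tests that both fit the effectiveness sentence, and it needs no assumption that any significant result wins.

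**Conclusion.** The analysis is fixed ambiguously. The time point for effectiveness is given, the deciding test is not, and the trial is sized on a contrast that is none of the listed between-group tests.

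The firmest measure of the problem is the 20% disagreement between the post-training and change-score tests at d = 0.5. It rests on 63 per group, rho = 0.7 and the design effect applied at post-training only. Across the listed tests, power runs from about 10% to 97% if the effect is confined to post-training; a sustained effect would narrow that gap. The false-positive figures are conditional: about 9% to 14% if any of two to four tests may count, near 5% if one decides. None of these calculations includes the planned walking-speed covariate, so they describe the scale of the problem rather than the exact tests to be run.

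This should be corrected before unblinding, but it does not put the design itself in doubt.

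**What to change.** State under Data management and statistical analysis that effectiveness is decided by one contrast at two-sided alpha 0.05: Feedback minus No-feedback in affected-limb treadmill MTC magnitude at the post-training assessment, estimated from one model. Say how baseline MTC enters that model, for example as a covariate. Label the change-score analysis, the ANOVA group effect, the omnibus Group x Time test and the post-hoc comparisons as supportive, with no claim of effectiveness resting on them alone.

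This takes one or two sentences and needs no new data. It calls for no more participants either: under the plan's own inputs, 63 per group gives about 97% power for the baseline-adjusted contrast. The downside is that effectiveness can no longer be claimed from a supportive test if the named contrast is not significant.

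### The five-visit repeated measures ANOVA, in its standard form, rests the retention contrasts (and possibly the post-training contrast) on participants seen at every visit; a mixed model would use all observed MTC

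*Protocol article*

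**What the plan says.** The Data management and statistical analysis section plans group comparisons together with "repeated measures ANOVA of the intervention groups and change scores, with post-hoc comparisons where relevant" for treadmill MTC, with walking speed as covariate. Treatment group is the between-subject factor, "with Time (pre-training baseline, post-training, one month, three months, and six months) being the within-subject factor".

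The same section lists what the analyses are for. Effectiveness is judged at one visit: "Between-group comparisons of MTC post-training will reveal effectiveness of the biofeedback gait training method in improving MTC". Retention is judged from the one, three and six month data. The text does not say whether the post-training and change-score comparisons are separate analyses or contrasts within the five-level model.

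The Sample size calculations section uses two visits only, "across the two time points (baseline and after training"), with "2 × 2 repeated measures design, α = 0.05, power = 0.85, correlation = 0.7". It then allows for loss: "To allow a 20% drop-out, we shall initially recruit 75 participants per group".

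**The concern.** A classical repeated measures ANOVA with a five-level within-subject factor needs five values per participant. Someone with baseline and post-training MTC who misses only the three-month visit drops out of the whole model. Visits that play no part in the sizing would then help decide whose data count.

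Two things are at stake.

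- **Precision.** Observed MTC values are set aside.
- **Bias.** Those with complete rows may differ from those without. Only Feedback participants train against a displayed MTC target, so a poor gain is visible to them and not to controls. A link between response and leaving that differs by arm is therefore conceivable, though the documents give no evidence of one.

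**Working it through.** **1. Reproduce the plan's figure.** Inputs from Sample size calculations: f = 0.25, m = 2 time points, correlation ρ = 0.7, α = 0.05, power 0.85. The between-groups repeated measures F test has

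λ = f² · N · m / (1 + (m − 1)ρ), with 1 and N − 2 degrees of freedom.

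For N = 126, λ = 0.0625 × 126 × 2 / 1.7 = 9.26 and power is 0.855. This is the smallest even N that reaches 0.85, so the stated 126 is reproduced. The same formula is the yardstick below.

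**2. Planned 20% loss.** 150 × 0.80 = 120 complete rows; λ = 0.0625 × 120 × 2 / 1.7 = 8.82; power 0.838. How much of this is due to the method depends on when people leave, which the article does not say.

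- If all leave after post-training, 150 people have post-training MTC (λ = 11.03, power 0.910), and the complete-row model sets 30 of them aside.
- If all leave during training, their post-training value is absent under any method, and complete-row deletion costs the post-training contrast nothing extra.

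**3. Sporadic missed visits added (assumption: 5% at each of the four post-baseline visits).** Complete rows: 120 × 0.95⁴ = 97.7, about 98; power 0.757. With the 20% drop-out spread evenly over the four visits, about 5% have left by post-training: 150 × 0.95 × 0.95 = 135.4, about 135 people with post-training MTC; power 0.879.

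**4. Range.** The documents give no visit-level rates. If each post-baseline visit is missed independently, with no other drop-out:

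| Missed per visit | Complete rows | Power | Seen at post-training | Power |
|---|---|---|---|---|
| 5% | 122 | 0.845 | 142 | 0.895 |
| 10% | 98 | 0.759 | 135 | 0.879 |
| 15% | 78 | 0.659 | 127 | 0.860 |
| 20% | 61 | 0.552 | 120 | 0.838 |

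**5. Bias, by simulation.** Assumptions: 75 per arm, correlation 0.7, about 20% to 25% incomplete, drop-out driven by the observed MTC gain.

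- True effect 0.5 SD, missingness unrelated to response: completers' estimate 0.50.
- Same dependence on response in both arms, centred within arm: 0.50.
- Dependence in the Feedback arm only: 0.57, 0.62 and 0.73 SD for weak, moderate and strong dependence.
- No true effect, Feedback arm only, log-odds 1 to 1.5 per SD: bias of roughly +0.1 to +0.17 SD. At the article's SD of 0.77 cm this is 0.1 × 0.77 = 0.08 cm to 0.17 × 0.77 = 0.13 cm. Two-sided false-positive rates ran from about 9% to 21%, depending on how drop-out was generated. Using all observed post-training values, or a mixed model, bias was about zero. That is expected, because drop-out depended only on observed values.

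**6. Sphericity.** With correlations that decay over visits, an uncorrected Group × Time test rejected about 7% of the time under the null, against a nominal 5%.

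**The case against.** The article nowhere says that only complete cases are analysed; that is inferred from the named method. It lists group comparisons, change scores and a post-training comparison beside the ANOVA, and sizes the trial on baseline and post-training alone. This fits a two-visit efficacy comparison on everyone seen at post-training, with the five-level model serving retention. A reader might infer that the plan discards its own post-training data and overstates the biofeedback effect. The documents do not support that: it is one of two open readings, and the overstatement also needs a drop-out pattern that nothing in the article indicates.

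The power loss at the planned 20% is also slight. In a simulation of the more sensitive baseline-to-post contrast (true effect 0.5 SD, 20% drop-out plus 5% sporadic missed visits), complete rows still gave about 0.90. The sphericity point presumes an uncorrected test that the article never specifies, and such corrections are commonly left to a fuller document.

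All of this stands as a limit on size. It does not remove the point. The model and its five levels are fixed in the text, so this is not missing detail, and even on the favourable reading the retention contrasts still rest on complete rows.

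**Conclusion.** The concern holds in limited form. The five-level ANOVA, run conventionally, bases the 1, 3 and 6 month contrasts on complete rows. It does the same to the post-training contrast only if that contrast is taken from this model, which the text leaves open.

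- **Power.** Small at the planned loss: 0.838 with 120 complete rows, against a 0.85 target and at best 0.910. Material only if missed visits accumulate beyond that: 0.757 against 0.879 at an assumed 5% sporadic missing per visit.
- **Bias.** None if leaving is unrelated to response. It requires the link between leaving and response to differ between arms, or to act on arms whose responses differ. The figure of roughly +0.1 to +0.17 SD belongs to an assumed strong dependence in the Feedback arm only; it is not a forecast for this trial.
- **Sphericity.** Secondary.

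The change is worth making because it is specific, clearly better for the retention question and almost free.

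**What to change.** In Data management and statistical analysis, replace the five-level repeated measures ANOVA with a linear mixed model fitted by REML to every observed treadmill MTC value. Use group, visit and group × visit as fixed effects, walking speed as already planned, and an unstructured within-person covariance. Take the Feedback minus No-feedback contrast at post-training from this model, stating that it uses all participants seen at that visit, and take the 1, 3 and 6 month contrasts from the same model. Keep the complete-row ANOVA, with a sphericity correction, as a sensitivity analysis.

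The cost is a sentence or two of wording and standard software, with no extra participants, visits or measurements. Two drawbacks should be accepted openly: the main result no longer appears as a classical ANOVA table, and the model is valid only under missing at random. If leaving depends on unobserved MTC, it can be biased too.

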## Discussion

This innovative study will evaluate the impact of augmented sensory information for improving gait function, specifically foot-ground clearance, via visually presented biofeedback. The research findings will contribute to the broader falls prevention initiative by demonstrating the effectiveness of toe clearance biofeedback in making walking safer. It will also confirm whether faded feedback enhances learning by demonstrating how performance is affected immediately following training and whether it can be retained in the long term. If shown to be effective, there will be opportunities for biofeedback-training applications to other gait-impaired clinical populations. The project’s findings will contribute to understanding how stroke-related changes to sensory and motor processes influence the tripping risks of everyday walking. The protocol is, however, limited to people with chronic stroke capable of walking on a treadmill due to the continuous real-time feedback used for gait training.

## Trial status

Recruitment began on 27 April 2017 with Protocol Version 6 dated 16 September 2016. Protocol Version 8 dated 20 June 2018 is currently in use following minor amendments not affecting the implementation of the project protocol. Recruitment is expected to be completed by 31 December 2020. Any important protocol modifications will be formally communicated to relevant parties by the chief investigator and the Protocol Version updated.

## Abbreviations

COPE: Centre of pressure excursion
ES: Effect size
FIM: Functional independence measure
FROP-Com: Falls Risk for Older People in the Community
MTC: Minimum toe clearance
RTC: Randomized controlled trial
SD: Standard deviation
